### Exclusion criteria

● Pseudoaneurysm [23].

● Drug addiction.

● Patients with the following systemic diseases:

   serious coagulation dysfunction

   organ failure

   serious psychosomatic diseases

● HIV.

● Pregnant or lactating women.

● The person responsible for the patient refused to give consent to participate in this trial.

● Patient was participating in another randomized clinical trial for treatment of SAH.

### Withdrawal from the study

● Even if patients are included in the trial, the person responsible for the patient can withdraw informed consent at any time.

● If severe adverse events occur, patients can be withdrawn from the study on consideration of their personal safety.

● If the person responsible for the patient decides to abandon treatment, patient will be withdrawn as they do not fully participate in the trial.

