### Follow-up

Two investigators (senior neurosurgeons) that are not involved in allocation or treatment will follow up of all patients at 1, 3, and 6 months after neurosurgical clipping. Primary outcomes of the trial are the Extended Glasgow Outcome Scale and the Modified Rankin Scale (mRS) at 6 months after aneurysm clipping. Both scales will be measured with structured interviews. The secondary indicators include the Barthel Index and mortality.

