### Adverse and severe adverse events

Adverse events (AE) are defined as any unwanted incidents in patients during the trial. Coma was excluded as an AE, because all patients enrolled in the trial were in poor neurological condition on admission. Serious adverse events (SAE) are defined as death or vegetative state. Both AEs and SAEs will be recorded on the CRF, including the details of the event, the correlation with the trial, the start and the end date, treatments used, their efficacy and outcomes. In the case of AEs and SAEs, the BMEC and QMB will be informed within 24 hours after the SAEs are detected .

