### Statistical analysis

Intention-to-treat (ITT) analysis and per-protocol (PP) analysis will be performed. The level of significance required for 80% power and a 5% (2-sided) significance level will be used. All data will be analyzed by the statistical analysis using Statistical Package for Social Sciences software (SPSS), version 17.0. Quantitative variables will be analyzed using t-test. Chi-square test and Fisher’s exact test will be used to analyze categorical variables. To analyze the outcome at 6 months after surgery, a comparison between groups will be made using the Mann–Whitney U-test and the significance of observed differences in outcome will be assessed with the Fisher’s exact test. Survival analysis will be further compare mortality between groups. Logistic regression will be used to adjust the effect of multivariable.

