**Figure 1 F1:**
[figure not shown]
The study considerations of our trial.

This trial was elaborately designed to avoid several forms of bias and improve accuracy. The experience of presciously authors was noted and was merged into our design of the trial [19-21]. We will record all treatment results and surgical results, but only treatment results will be utilized for analysis. This will avoid selection bias, because all treatment results will include patients that may die from rebleeding, vasospasm or other complications, when awaiting surgery, especially those patients assigned to the intermediate or late surgery groups. Patients in intermediate or late surgery groups will receive emergency surgery when space-occupying hematoma, midline shift and emergency surgery indications are confirmed. Bias will be solved through the use of ITT analysis.

Although previous reports have demonstrated that patients in poor condition on admission within 6 hours after the onset of SAH achieved better outcomes than patients admitted later [12,26], this trial will enroll all the patients with PGASAH on admitted within 72 hours. As one of the largest hospitals in China, the number of patients admitted within 6 hours after the onset of SAH was relatively small in our department. More patients are transferred from other cities, even from the outlying areas in the west of China, and which takes time. The trial was not designed to include a small number of patients, but to include the overwhelming majority of the patients.

Neurosurgeon experience is an important factor in outcome after SAH. More than 4,000 surgeries are completed in our Department of Neurosurgery every year. Every neurosurgeon participating in the trial has accumulates experience of more than 200 neurosurgical clippings yearly, thus ensuring that every surgery will be performd to a high standard.

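### Patients whose treatment is abandoned must be withdrawn from the study, and nothing shown keeps them in follow-up or in the intention-to-treat set that is meant to solve bias

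*Protocol article*

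**What the plan says.** The section Withdrawal from the study has three rules. The first is the right to withdraw consent, which is not in question here. The second is permissive: "If severe adverse events occur, patients can be withdrawn from the study on consideration of their personal safety". The third is mandatory and gives its reason: "If the person responsible for the patient decides to abandon treatment, patient will be withdrawn as they do not fully participate in the trial".

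The section Adverse and severe adverse events adds: "Serious adverse events (SAE) are defined as death or vegetative state". Under Follow-up, the article states: "Primary outcomes of the trial are the Extended Glasgow Outcome Scale and the Modified Rankin Scale (mRS) at 6 months after aneurysm clipping". It continues: "The secondary indicators include the Barthel Index and mortality".

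Under Statistical analysis: "Intention-to-treat (ITT) analysis and per-protocol (PP) analysis will be performed". In the Discussion, after Figure 1, the authors say they will analyse the results of the whole treatment course rather than of surgery alone, "because all treatment results will include patients that may die from rebleeding, vasospasm or other complications, when awaiting surgery". The paragraph ends: "Bias will be solved through the use of ITT analysis".

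**The concern.** An ITT analysis needs an outcome for every randomised patient. The mandatory rule takes patients out of the study for incomplete participation, which is exactly what ITT is meant to disregard. If their 6-month outcomes are not collected, analysing the remaining patients as allocated does not bring those outcomes back.

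The loss would hardly be random. The Background puts mortality without surgery above 90%, so patients whose treatment is abandoned before surgery are likely to do badly. The intermediate and late arms leave more time for this, and the Discussion itself expects deaths before surgery especially in those arms. Only the observer is blinded, so relatives and treating staff can know the allocation when they decide. If more poor outcomes drop out of the waiting arms, delayed surgery looks better than it is on both primary scales, and on mortality too where deaths are not recorded.

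**Working it through.** **1. What the plan gives.** It states no withdrawal rate, so there is no figure to reproduce on this point. The nearest one is the increase from 88 to 99 for loss to follow-up: 99 − 88 = 11 patients, and 11/99 = 11.1%. That allowance protects numbers. It does not protect against selective loss.

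**2. The statements side by side.**

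- *Abandonment rule:* mandatory, and it ends study participation rather than only the treatment.
- *Adverse-event rule:* optional, tied to personal safety. The events defined as serious coincide with the lowest levels of the Extended Glasgow Outcome Scale (GOSE), and death is also a secondary outcome.
- *Retention:* no statement says that withdrawn patients are followed to 6 months or kept in the ITT set. Visits are timed from clipping, so a patient who leaves before surgery has no dated outcome visit.
- *Discussion:* deaths before surgery are to count, and ITT is to solve bias.

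The first and last statements pull in opposite directions. Whoever builds the analysis dataset could follow either.

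**3. Illustration.** Inputs:

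- True unfavorable rate p = 50% in both arms (Sample size section), so there is no real difference.
- Withdrawn share w per arm: not in the documents; assumed.
- Every withdrawn patient is unfavorable and unscored: assumed.

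Observed rate = (p − w)/(1 − w).

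| Arm | w | Calculation | Observed |
|---|---|---|---|
| Early | 5% | 0.45/0.95 | 47.4% |
| Late | 15% | 0.35/0.85 | 41.2% |
| Late, more extreme | 25% | 0.25/0.75 | 33.3% |

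The false advantage for late surgery is 47.4 − 41.2 = 6.2 points, or 47.4 − 33.3 = 14.1 points (14.0 before rounding) in the extreme case. The planned difference is 30 points.

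**4. In patients.** With 33 per arm (equal allocation assumed), 5% is about 2 patients (1.65), 15% about 5 (4.95) and 25% about 8 (8.25).

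**5. When the false difference vanishes.** If w is the same in both arms, the formula gives the same observed rate in both. If withdrawn patients are no worse than the rest, so that half are unfavorable, the observed rate is (0.50 − 0.50w)/(1 − w) = 50% for any w. The distortion therefore needs withdrawal that is related to prognosis and also unequal between arms.

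**The case against.** A reader might infer that the rules remove the worst primary outcomes and defeat the ITT analysis. The documents do not support that as a statement of fact.

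- The withdrawal section never says that follow-up stops or that data are discarded. The Follow-up section speaks of all patients, allocation cannot be changed after randomisation, and a survival analysis of mortality is planned.
- The adverse-event clause is optional and concerns the patient's safety, which cannot apply to someone who has died. Serious events and their outcomes go on the case report form, so a recorded death can still be scored. The withdrawal rule also says *severe* where the definition says *serious*. The heading above the definition suggests they are the same term, but this is not certain.
- The Discussion commits to counting deaths before surgery.

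It is also tempting to say that the per-protocol set has the same fault. The article names that analysis but does not define the set, and an article commonly leaves the definition to the full protocol or analysis plan. No finding can rest on it.

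The size is assumed, not observed. At 33 per arm, the standard error of a difference between two 50% rates is √(2 × 0.25/33) = 0.123, so 6.2 points is about half a standard error. The 14-point case needs about 8 losses in one arm, against an allowance of 11 for the whole trial. Unequal abandonment between arms is plausible but not shown, and the Discussion places the main rebleeding risk in the first 6 to 12 hours, which touches every arm. Abandonment by the responsible person may sometimes amount to withdrawn consent, in which case follow-up cannot be assumed.

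These points reduce the adverse-event clause to a possible route of loss. They do not answer the abandonment rule, which is mandatory, gives incomplete participation as its reason, and has no retention statement beside it.

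**Conclusion.** The concern holds for the abandonment rule. As written, it conflicts with the Discussion's reliance on ITT, and following it could lose outcomes that are probably poor and perhaps more often from the delayed arms. Under the stated assumptions, the false advantage for late surgery is about 6 points with 5% against 15% withdrawn and about 14 points with 5% against 25%. It is zero if withdrawal is equal across arms or unrelated to outcome. The direction depends on abandonment being more frequent where the wait is longer, which the documents make plausible but do not establish. Withdrawal after a severe adverse event adds to the risk only if such patients are in fact removed and left unscored.

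**What to change.** Reconcile the withdrawal section with the Discussion by separating the end of treatment from the end of follow-up:

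- Abandoned treatment or an adverse event ends the allocated intervention only. The clinical decision itself is left as it is.
- Only withdrawal of consent for follow-up ends data collection. Where treatment is abandoned, record whether that consent was also withdrawn.
- Every other randomised patient is followed to 6 months, with a stated time origin for those who never have clipping.
- All randomised patients are analysed in the allocated arm, with death scored as the worst category on GOSE and on the modified Rankin Scale.
- The main conclusion rests on the ITT analysis.

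The cost is a change of wording and a few more follow-up contacts by the existing investigators.

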### Randomization

Minimization, a kind of balance randomization method, will be used in this trial. Characteristics of patients who meet the selection criteria will be submitted to random analyst. After the data is entered into a computer, patients will be randomly divided into an early, intermediate or late surgery group using specialized minimization software. Once random allocation has been determined, groups cannot be changed. Stratified randomization will be employed. Four stratification factors will be applied to achieve balanced randomization: 1) patient’s age, 2) gender, 3) Hunt & Hess grading and 4) the size of aneurysm.

### Blinding

Because of the nature of the study, only the observer can be blinded. In order to prevent bias, the following measures will be taken. 1) Patient characteristics will be collected and evaluated by two special doctors who are not involved in any other stage of the trial. 2) Patient randomization will be performed by an independent random analyst. 3) Patient outcomes will be followed up by two special investigators who are not involved in the allocation or the treatment process. 4) Statistical analysis will be performed by a special statistician who did not participate in the implementation of the study. 5) Because of the sequence of the Case Report Form (CRF), each stage of the study will be completed in a specific order by the allocated individuals. Patient characteristics will be the first section completed, followed by the independent random analyst, subsequently the neurosurgeons will describe the treatment procedure, complications, adverse and severe adverse events in the CRF, the last will be the two special investigators. All the researchers will submit a copy of their original data to the Quality Monitoring Board (QMB), before the CRF is available.

### Treatment

All patients with SAH admitted in poor neurological condition (Hunt & Hess IV–V) will receive effective treatment, according to guidelines for the management of aSAH that published in 2012[24]. Aggressive resuscitation, including intubation, ventilation, and mannitol administration, will be implemented in the emergency department. CT scan will be performed as soon as possible after admission. Intracranial pressure (ICP)-monitoring sensor implantation (Codman Group Inc) will be performed on all identified patients after admission to continuously measure ICP. If aSAH-related hydrocephalus is confirmed by CT scan, both external ventricular drain (EVD) and ICP-monitoring sensor implantation will be performed. ICP-targeted treatment will be given to patients with elevated ICP. These therapeutic measures include head elevation to 30°, hyperosmolar therapy, tracheal intubation, sedation and analgesia, and mild hypothermia. Neurosurgical clipping will be performed at different times, according to the randomized grouping. Aneurysms of the anterior circulation were approached through the standard pterional craniotomy and all aneurysms were obliterated by direct clipping. Postoperatively, patients will return to the neurosurgical intensive care unit (NICU) for intensive monitoring.

### Follow-up

Two investigators (senior neurosurgeons) that are not involved in allocation or treatment will follow up of all patients at 1, 3, and 6 months after neurosurgical clipping. Primary outcomes of the trial are the Extended Glasgow Outcome Scale and the Modified Rankin Scale (mRS) at 6 months after aneurysm clipping. Both scales will be measured with structured interviews. The secondary indicators include the Barthel Index and mortality.

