**Methods/design:**

Ninety-nine patients meeting the inclusion criteria were randomly assigned into three treatment groups. The early surgery group received operation within 3 days after onset of subarachnoid hemorrhage (day of SAH = day 1); the intermediate surgery group received operation from days 4 to 7, and surgery was performed on the late surgery group after day 7. Follow-up was performed 1, 3, and 6 months after aneurysm clipping. Primary indicators of outcome included the Extended Glasgow Outcome Scale and the Modified Rankin Scale, while secondary indicators of outcome were assessed using the Barthel Index and mortality.

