### Overview of study design

West China hospital receives the most patients with PGASAH in western of China. This study is a prospective, single-centre, observer-blinded, randomized controlled trial with stratification according to the patient’s age, gender, Hunt & Hess grading and the size of aneurysm. Ninety-nine patients meeting the criteria will be randomly assigned into three treatment groups. The early surgery group will receive operation within 3 days after onset of SAH, the intermediate surgery group from days 4 to 7, and the late surgery group after day 7 post-SAH.

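### Visits and both primary scales are timed from aneurysm clipping, so randomised patients who are never clipped have no 6-month date, and the arms are assessed at different times after hemorrhage

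*Protocol article*

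**What the plan says.** Three places in the protocol article set the outcome clock, and all three use the operation.

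- Abstract, Methods/design: "Follow-up was performed 1, 3, and 6 months after aneurysm clipping".
- Follow-up: the two investigators "will follow up of all patients at 1, 3, and 6 months after neurosurgical clipping", and "Primary outcomes of the trial are the Extended Glasgow Outcome Scale and the Modified Rankin Scale (mRS) at 6 months after aneurysm clipping".
- Statistical analysis: the main comparison is introduced with "To analyze the outcome at 6 months after surgery".

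The date of the operation is what is randomised. Overview of study design states: "The early surgery group will receive operation within 3 days after onset of SAH", then "the intermediate surgery group from days 4 to 7, and the late surgery group after day 7 post-SAH". The abstract counts the day of hemorrhage as day 1.

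On patients who do not reach surgery, the Discussion says that "all treatment results will include patients that may die from rebleeding, vasospasm or other complications, when awaiting surgery", and names the intermediate and late groups as those most affected. It relies on intention-to-treat to deal with the bias. The Statistical analysis section plans both intention-to-treat and per-protocol analyses. On mortality it adds: "Survival analysis will be further compare mortality between groups". It gives no time origin for that analysis.

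**The concern.** In a trial of surgical timing, the date of surgery is a consequence of allocation. A clock that starts there has three weaknesses. It does not start at all for patients who never reach surgery. It starts later in the delayed arms by design. And patients in those arms must survive the wait before it starts.

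Deaths while waiting are a cost of delay that the Discussion itself anticipates. An endpoint definition that cannot be applied to those patients leaves the key comparison open to handling that differs by arm, and the likely error favours late surgery. This is not a detail that a condensed article leaves to a fuller document: the article states the primary time point, and states it in a form that does not fit every randomised patient.

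**Working it through.** The plan gives no figure on this point to reproduce. The check has three steps.

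**1. Who has a 6-month date?**

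| Randomised patient | Clipping date | 6-month date under Follow-up | Included under the Discussion or intention-to-treat |
|---|---|---|---|
| Clipped, alive at 6 months | yes | yes | yes |
| Clipped, dies afterwards | yes | yes | yes |
| Dies before clipping | no | none | yes, explicitly |
| Alive, never clipped | no | none | yes, by intention-to-treat |

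The last two rows are the defect. The article gives no other origin and no rule for either row.

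**2. How far apart are the arms assessed?**

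Inputs: the surgery windows (Overview of study design) and day of hemorrhage = day 1 (abstract). I take 6 months as 183 days and 1 month as 30 days. Clipping on day *d* is *d* − 1 days after hemorrhage, so a visit *m* days after clipping falls *m* + *d* − 1 days after hemorrhage.

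- Early, days 1 to 3: 183 to 185 days at the 6-month visit.
- Intermediate, days 4 to 7: 186 to 189 days.
- Late, day 8 onward: 190 days or more, with no upper limit.

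The smallest late-versus-early gap is 190 − 185 = 5 days. The table compares early clipping on day 2 (184 days at 6 months, 31 days at 1 month) with assumed late clipping days:

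| Late clipping day (assumed) | Gap, days | Share of 184 days | Share of 31 days |
|---|---|---|---|
| 8 | 6 | 3.3% | 19% |
| 14 | 12 | 6.5% | 39% |
| 21 | 19 | 10.3% | 61% |
| 28 | 26 | 14.1% | 84% |

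These gaps apply to patients clipped within their assigned window. The Discussion also allows emergency surgery in the delayed arms.

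**3. What if only clipped patients were assessed?**

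This step is conditional on a literal use of the definition. Let *m* be true mortality and *w* the share dying before clipping, with everyone else clipped. Observed mortality is (*m* − *w*)/(1 − *w*). The documents give neither *m* nor *w*. Assume *m* = 40% in both arms.

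- Early, *w* = 2%: 0.38/0.98 = 38.8%.
- Late, *w* = 5%: 0.35/0.95 = 36.8%.
- Late, *w* = 15%: 0.25/0.85 = 29.4%.
- Late, *w* = 25%: 0.15/0.75 = 20.0%.

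From unrounded values, the false advantage for delay is 1.9, 9.4 and 18.8 points.

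The same formula can be used with the 50% unfavorable rate in the Sample size section, assuming no pre-clipping deaths in the early arm. The late arm then shows 0.40/0.90 = 44.4%, 0.30/0.80 = 37.5% or 0.20/0.70 = 28.6% for assumed waiting deaths of 10%, 20% or 30%. The false advantage is 5.6, 12.5 or 21.4 points, against a planned difference of 30.

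**The case against.** The strongest reply is that the authors saw the problem. The Discussion says deaths while waiting will be included, Follow-up refers to all patients, and intention-to-treat is planned. Both primary scales have a category for death, so a patient who dies before surgery can be scored without a visit date. Step 3 therefore describes an analysis that the Discussion rejects.

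Much of this stands. A reader might infer that the plan drops waiting deaths. The documents do not support that; they support only that the written endpoint does not define an assessment date for these patients. A reader might also infer that mortality is to be counted from clipping. The survival analysis states no origin, so bias there is a risk and not a stated plan. Nor does every death lack a date: patients who die after clipping have one. The timing gap is modest at the 6-month primary assessment, and nothing in the documents shows that a gap of that size moves either scale materially.

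The reply does not remove the defect. Intention-to-treat keeps patients in their assigned arm, but it does not supply an outcome that the definition leaves blank. Survivors who are never clipped cannot be handled by scoring a death, and no assessment is defined for them. The Follow-up and Statistical analysis sections still need to say what the Discussion intends.

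**Conclusion.** The point holds as a badly fixed time origin that conflicts with the protocol's own intent. Randomised patients who die before clipping, or survive without it, have no defined 6-month date. Patients clipped in their assigned windows are assessed at different times after hemorrhage: at least 5 days later in the late arm, with no upper bound. For the assumed late clipping days, that is about 3% to 14% of the early arm's elapsed time at 6 months and 19% to 84% at 1 month. The missing outcome definition is the more serious part.

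The 38.8% versus 29.4% mortality contrast rests on assumed rates and arises only if unclipped patients are left out, contrary to the Discussion. A reader might go further and conclude that the trial's answer on timing would be reversed. The calculation does not show that: it assumes no true difference and shows only the direction and possible size of a distortion.

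**What to change.** In the abstract, Follow-up and Statistical analysis sections, replace clipping or surgery with randomisation as the reference point for timing. Then state the following.

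- The Extended Glasgow Outcome Scale and the modified Rankin Scale are assessed at 1, 3 and 6 months after randomisation in every randomised patient, clipped or not.
- Death, before or after surgery, is scored as the worst category on both scales.
- The survival analysis runs from randomisation.

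The article limits onset to admission to 72 hours but sets no limit from admission to randomisation. That interval precedes allocation, however, so it does not differ by arm by design.

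The change is a short amendment to visit scheduling and definitions and leaves the sample size as it is. Its cost is that late-arm visits fall sooner after surgery. For example, for a patient randomised on day 1 and clipped on day 21 (both assumed), the visits come 183 − 20 = 163 days after clipping at 6 months and 30 − 20 = 10 days at 1 month. The 1-month results should be read with that in mind.
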